Train-the- trainer workshop	1-day workshop for clinical leads: discussed Australasian Bronchiolitis Guideline and evidence supporting recommendations, qualitative study identifying the facilitators and barriers of bronchiolitis management, implementation, and the development of interventions. Clinical leads received demonstrations on how to deliver educational interventions to their staff, outlines of study data timelines and requirements, and enabled planning time for clinical leads.	One-day workshop providing bronchiolitis intervention materials, with up to four clinical leads (medical and nursing) invited to attend. Discussion on what the aims of education materials were. Individual hospital data from the cluster RCT was presented (2014-2017). Feedback in relation to similar hospitals.
Educational intervention delivery	Key findings from qualitative study were presented in a PowerPoint with scripted messages stating use of behaviour change techniques most likely to effect change. Clinical Leads oversaw education delivery to medical and nursing staff using PowerPoint presentation. Within first month, aimed to educate 80% of staff and to ensure all staff educated ongoing education provided throughout duration of study.	PowerPoint presentation which was the same as presentation provided to the intervention hospitals.
Use of other educational materials	Clinical leads locally delivered promotional materials, evidence factsheets, clinician training video, and parent/caregiver information.	Education materials that were provided to the intervention hospitals.
Audit and feedback	Monthly audits of the first 20 bronchiolitis presentations, with report providing comparison between individual hospital results and top-performing site. Clinical leads disseminated report to their staff in written and verbal format; action planning with target setting encouraged.	Audit form and own hospital results from trial (4 years of data).
Ongoing facilitation	Weekly contact between clinical leads and study leads. Opportunities to ask questions via email.	Nil.

^a^delivered at trial completion in November 2018

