Findings of the PREDICT Bronchiolitis KT Study demonstrated that, when compared with control hospitals, intervention hospitals significantly improved adherence in management of bronchiolitis during the acute care period (first 24 hours of hospital presentation) for the five key low-value practices as per Australasian Bronchiolitis Guideline recommendations (14.1% adjusted risk difference, 95% CI, 6.5-21.7%; *P* < .001) [4, 34]. Specifically, during the acute care period (first 24 hours of hospital presentation), adherence to the Australasian Bronchiolitis Guideline recommendations with no use of salbutamol, glucocorticoids, antibiotics, adrenaline and CXRs, was 85% (95% CI, 82.6-89.7%) in the intervention group hospitals compared with 73% (95% CI, 65.3-78.8%) in the control group hospitals [4, 34]. At trial completion (November 2018), up to four nurses and doctors from each of the 13 control hospitals attended a 1 day workshop where they were given training and provided with intervention materials (Table 1). However, no on-going facilitation was provided.

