#### Outcome measures for quantitative study

Primary Outcome:Adherence with all five Australasian Bronchiolitis Guideline Recommendations (composite outcome) known to have no benefit (salbutamol, glucocorticoids, antibiotics, adrenaline and CXR) when an infant presents with bronchiolitis in the acute care period (first 24 hours of hospitalisation) at two- years (2019) following the completion of the PREDICT Bronchiolitis KT Study in intervention hospitals [34];

Secondary Outcomes:2.Adherence with all five Australasian Bronchiolitis Guideline Recommendations (composite outcome) known to have no benefit (salbutamol, glucocorticoids, antibiotics, adrenaline and CXR) when an infant presents with bronchiolitis in the acute care period (first 24 hours of hospitalisation) at one- year (2018) following the completion of the PREDICT Bronchiolitis KT Study in intervention hospitals [34];3.Adherence with all five Australasian Bronchiolitis Guideline Recommendations (composite outcome) known to have no benefit (salbutamol, glucocorticoids, antibiotics, adrenaline and CXR) when an infant presents with bronchiolitis in the acute care period (first 24 hours of hospitalisation) at 3a) one- year (2019) following provision of study materials, study results, and ‘Train the Trainer’ education (composite of all five practices) [4, 34]; and 3b) one- year (2018) following the completion of the PREDICT Bronchiolitis KT Study in control hospitals [4, 34].

The periods of one- and two- years following delivery of the intervention will be measured from the post-trial completion date of 30th November 2017.

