### Data analysis

Analysis of the data from the medical record audit will occur at the patient level, according to the group (intervention/control) that hospitals were randomly allocated in the previous study [4]. Absolute and relative frequencies of no use of all five low-value practices will be calculated. Means and standard deviations or medians and interquartile range will be used to present continuous outcomes. The proportions of no use of all five low-value practices and its 95% confidence intervals will be calculated and presented by study group. *Exploratory Objectives* will be run to estimate the marginal differences in proportions of no use of all five low-value practices between the study groups, using Generalised Linear Mixed (GLM) [34]. If the GLM models do not converge, logistic regression with a clustered-robust standard error (hospital level) will be used to calculate odds ratios. *Exploratory Objectives* will examine adherence to the five individual practices (i.e, no use of all five low-value practices); difference between intervention and control groups in 2019; difference between intervention and control groups in 2018; and trends over time (Table 3).

**Table 3 Tab3:** Exploratory objectives

To determine:	
• The proportion of infants presenting to hospital with bronchiolitis in the acute care period^a^, at intervention group hospitals, who received care that adhered with each of the five individual Australasian Bronchiolitis Guideline Recommendations known to have no benefit^b^: a) two- years (2019) following delivery of a targeted intervention [34]; and b) one- year (2018) following delivery of an intervention designed to promote evidence-based practice adherence [34];	
• The proportion of infants presenting to hospital with bronchiolitis in the acute care period^a^, at control group hospitals, who received care that adhered with each of the five individual Australasian Bronchiolitis Guideline Recommendations known to have no benefit^b^: a) two- years (2019) following delivery of an intervention designed to promote evidence-based practice adherence [4, 34]; and b) one- year (2018) following delivery of bronchiolitis intervention [4, 34];	

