• The difference between control and intervention group hospitals in the proportion of infants presenting to hospitals with bronchiolitis who received care that adhered with each of the five individual Australasian Bronchiolitis Guideline Recommendations known to have no benefit^b^ in the acute care period: a) two- years (2019); following the completion of the PREDICT Bronchiolitis KT Study [4, 34]; and b) one- year (2018); following the completion of the PREDICT Bronchiolitis KT Study [4, 34];	
• The difference between control and intervention group hospitals in the proportion of infants presenting to hospital with bronchiolitis who received care that adhered with all five Australasian Bronchiolitis Guideline Recommendations known to have no benefit^b^ in the acute care period: a) two- years (2019) following the completion of the PREDICT Bronchiolitis KT Study (composite outcomes of all five practices) [4, 34]; and b) one- year (2018) following the completion of the PREDICT Bronchiolitis KT Study (composite of all five practices) [4, 34];	
• The trends in the proportions of infants presenting to hospital with bronchiolitis who received care that adhered with each of the individual five Australasian Bronchiolitis Guideline Recommendations known to have no benefit^b^ yearly from 2014 to 2019 in the acute care period, at control and intervention group hospitals [34].	

^a^ First 24 hours of hospitalisation, ^b^ no use of: i) salbutamol, ii) glucocorticoids, iii) antibiotics, iv) adrenaline, and v) chest x-ray

An a priori definition of sustained improvements will be based on the 7% median improvement achieved in the PREDICT Bronchiolitis KT Study [4]. Practices will be defined as sustained when there is either a maximum of a seven percentage point decrease or any level of improvement (i.e. -7% to infinity) from the participating hospital’s individual post-implementation results based on a composite outcome of the five low-value practices of interest [4, 34].

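### The exploratory 2018 and 2019 between-group contrasts state no baseline term, and the 2014-2019 trend objective omits the composite; adjusting for pre-trial adherence could narrow an interval of about ±11 points at no data cost

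*Protocol article*

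**What the plan says.** **The contrasts.** The quantitative Data analysis section of the protocol article says that models will "estimate the marginal differences in proportions of no use of all five low-value practices between the study groups, using Generalised Linear Mixed (GLM) [34"]. If these do not converge, "logistic regression with a clustered-robust standard error (hospital level) will be used to calculate odds ratios". The contrasts are listed among the exploratory objectives: "difference between intervention and control groups in 2019; difference between intervention and control groups in 2018; and trends over time (Table 3"). No covariate is named for either model. Nor does the text say that the models are unadjusted.

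**The earlier data.** Table 1 records, for the control hospitals' workshop: "Individual hospital data from the cluster RCT was presented (2014-2017"). Table 3 plans trends "yearly from 2014 to 2019 in the acute care period, at control and intervention group hospitals", so earlier data are expected for both groups. That trend objective covers each of the five recommendations separately; the all-five composite is not in it. The parent trial ran from May to November 2017, so the pre-trial years are 2014 to 2016.

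**What the main conclusions rest on.** The primary outcome is composite adherence "at two- years (2019) following the completion of the PREDICT Bronchiolitis KT Study in intervention hospitals [34"], a single-group proportion. Improvement counts as sustained when a hospital falls by no more than seven points from its own post-implementation composite result. Aim (ii) asks whether adherence improved in control hospitals.

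**The concern.** These contrasts are the only planned analyses that use the randomised control hospitals as a comparator. With about 24 hospitals and an ICC of 0.11, nearly all their variance lies between hospitals, so auditing more infants per hospital would hardly help. A hospital-level covariate that predicts follow-up adherence could help, and the obvious one is the hospital's own pre-trial adherence. As written, pre-trial composite adherence has no stated use anywhere.

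Two things are at stake. The intervals may be wider than they need be, and chance differences between the groups' baselines stay in the estimate. Also, if covariates are left open, they may be chosen after the 2018 and 2019 data are seen, which is risky with so few clusters. The trend objective has a related gap: aim (ii) concerns adherence overall, but the yearly series that could supply its baseline is limited to the individual practices.

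**Working it through.** **Inputs.** From the article's Sample size section: ICC 0.11, coefficient of variation of cluster sizes (CV) 0.16, 12 intervention and about 12 control hospitals, m = 150 infants each (1800 per group), expected adherence 85%. From the parent-trial results: 85% v 73%. Not in the article: r, the correlation between a hospital's pre-trial adherence and its underlying 2018 or 2019 adherence. I assume a range of 0.3 to 0.8.

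**Step 1: reproduce the stated precision.**
- Design effect: DE = 1 + ((1 + CV²)m − 1) × ICC = 1 + (1.0256 × 150 − 1) × 0.11 = 17.81.
- Half-width = 1.96 × √(0.85 × 0.15 × 17.81 / 1800) = 6.96 points.

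This matches the article's 7%, so the inputs and formula are the ones it used.

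**Step 2: the unadjusted contrast on the same inputs.**
- SE = √(17.81 × (0.85 × 0.15 + 0.73 × 0.27) / 1800) = √(17.81 × 0.3246 / 1800) = 5.67 points.
- 95% half-width = 1.96 × 5.67 = 11.1 points, or 11.8 with t on 24 − 2 = 22 degrees of freedom.

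**Step 3: adjust for the hospital baseline.** The covariate reduces only the between-hospital part of the variance:

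DE_adj = (1 − ICC) + ICC × (1 − r²) × (1 + CV²) × m = 0.89 + 16.92 × (1 − r²).

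| Assumed r | DE_adj | SE relative to unadjusted | Half-width, 12 v 12 | Half-width, 13 v 13 |
|---|---|---|---|---|
| 0 (unadjusted) | 17.81 | 1.00 | 11.1 | 10.7 |
| 0.3 | 16.29 | 0.96 | 10.6 | 10.2 |
| 0.5 | 13.58 | 0.87 | 9.7 | 9.3 |
| 0.7 | 9.52 | 0.73 | 8.1 | 7.8 |
| 0.8 | 6.98 | 0.63 | 7.0 | 6.7 |

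Half-widths are in percentage points and use 1.96. Multiplying the whole SE by √(1 − r²) would give slightly smaller figures (9.6 at r = 0.5, 7.9 at r = 0.7), but that wrongly shrinks the within-hospital variance too.

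**Step 4: sensitivity to the control proportion.** If control hospitals had also reached 85%, the 12 v 12 half-width would be 9.8 points unadjusted and 9.4, 8.6, 7.2 or 6.2 adjusted. The relative gain is the same.

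**Step 5: can the parent trial's interval tell us r?** It reports "14.1% adjusted risk difference, 95% CI, 6.5-21.7"%, a half-width of (21.7 − 6.5)/2 = 7.6. Using ICC 0.11 with 13 v 13 hospitals and 3240 / 26 = 124.6 infants each gives DE = 14.95, SE = 5.47 and a half-width of 10.7 without adjustment. But the two group intervals (82.6-89.7 and 65.3-78.8) have half-widths of 3.55 and 6.75, and √(3.55² + 6.75²) is also 7.6. The article does not label those group intervals as adjusted. A true ICC below 0.11 would explain the narrower interval as well as baseline adjustment would, so r cannot be inferred from it.

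**The case against.** **Silence is not an unadjusted model.** An article condenses, and the covariate list of an exploratory model normally sits in the analysis plan. Reference [34] is cited for this very model and may contain it. This stands, and it makes the fix conditional. What remains is that the article fixes model, estimand, fallback and clustering level without a baseline term, and expressly limits the trend objective to the individual practices. The second is a stated scope, not an omission.

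**A reader might infer that the follow-up contrasts cannot be set against the parent trial's adjusted 14.1 points, or that an unchanged effect would be read as partly lost.** The article does not support this:
- Sustained improvement is judged against each hospital's own post-implementation result, not against 14.1.
- Both quantities are differences in proportions between randomised groups. Without adjustment the later one is noisier and open to chance imbalance, but it is of the same kind.
- The covariates behind 14.1 are not named.
- The article reports that adherence "was 85% (95% CI, 82.6-89.7%) in the intervention group hospitals compared with 73% (95% CI, 65.3-78.8%) in the control group hospitals", a 12-point gap. Whether these percentages are crude cannot be settled: the midpoints of their intervals, 86.15 and 72.05, differ by exactly 14.1.

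**The gain depends on an unknown correlation.** This also stands. At r = 0.3 the half-width falls by only half a point.

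**The 2019 contrast has a larger limit.** Table 1 dates the control hospitals' training to November 2018, so in 2019 the controls are no longer untouched. Baseline adjustment does not remove that. On that date the 2018 contrast is the cleaner comparison and benefits most from added precision.

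**Conclusion.** The point holds as a minor improvement in precision for exploratory analyses. On the article's planning inputs, the unadjusted between-group interval is about ±11.1 points. Adjustment for pre-trial composite adherence would bring it to between ±10.6 and ±7.0 for r from 0.3 to 0.8, that is, 4% to 37% off the standard error.

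This rests on 12 hospitals of 150 infants per group, a common ICC of 0.11, the same r in both groups, and an r that the article does not supply. It also assumes that the earlier records allow the composite to be built for each hospital, which the article implies but does not state. If the intervention made its hospitals more alike, r may be lower in that group and the gain smaller.

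The primary outcome, the secondary outcomes and the 7-point rule do not depend on this. Nothing here shows that the planned contrasts are biased or that they cannot be read alongside the trial's result.

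**What to change.** First check whether reference [34] or the analysis plan already specifies covariates for these models. If not:

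1. State that the 2018 and 2019 between-group models for the composite include each hospital's pre-trial (2014-2016) composite adherence as a covariate.
2. Report the standardised marginal risk difference with a small-sample (t-based) interval. Obtain the same quantity from the fallback logistic model by averaging its predicted probabilities under each allocation, since that model is now set to give only odds ratios.
3. Add the composite to the 2014-2019 trend objective, so that aim (ii) has a stated baseline on the measure used for the main conclusions.

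The cost is wording in the analysis plan and one or two of about 22 hospital-level degrees of freedom. No new data are needed if the earlier records hold the composite. If r proves low, little is gained and little is lost.

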## Background

In infants less than 1 year of age, the most common lower respiratory tract infection is bronchiolitis [1]. Bronchiolitis is caused by a viral infection, most frequently by respiratory syncytial virus and can be life-threating [2, 3]. In Australia and New Zealand, bronchiolitis is the leading cause of hospital admissions in infants under 6 months of age [2, 4, 5] accounting for 56% of Australian hospital admissions in infants less than 12 months of age, 7-9% of New Zealand hospital admissions in children 0 to 14 years of age [5–7], with infants from indigenous and deprived populations being most at risk [8].

Recommended management of bronchiolitis is well defined, comprising of supportive practices such as respiratory and hydration support [2, 3, 9]. There is strong evidence that five therapies and management processes, namely salbutamol, glucocorticoids, antibiotics, adrenaline and chest x-rays (CXRs) are ineffective or ‘low value’ and should not be used in the management of infants with bronchiolitis [1, 5, 10, 11]. Current international clinical practice guidelines, including the 2016 evidence-based guideline from Australia and New Zealand (Australasian Bronchiolitis Guideline) [1, 5] recommend against their use. Yet, variations in practice persist. An Australasian retrospective audit conducted at seven hospitals found that in 3856 infants who presented with bronchiolitis, 27-48% received at least one of the five low-value practices [12]. These results are consistent with the literature [4, 13], showing that even when evidence reveals no benefits, abandoning (i.e. de-implementing) low-value practices is often harder than implementing new practices [14–16]. In response to the variations in practice, we undertook the Paediatric Research in Emergency Departments International CollaboraTive (PREDICT) Bronchiolitis Knowledge Translation (KT) Study to improve bronchiolitis care. It demonstrated that use of targeted, theory-informed interventions significantly improved bronchiolitis care by de-implementing these five low-value practices by 14.1% (adjusted risk difference, 95% CI, 6.5-21.7%; *P* < .001) [4]. The focus of this current study is to determine if the change has been sustained (Fig. 1).

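### If the mixed model does not converge, the exploratory group comparisons switch to odds ratios, although their stated objectives are differences in proportions

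*Protocol article*

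**What the plan says.** The quantitative Data analysis section of the protocol article places the comparison of study groups under its exploratory objectives. A generalised linear mixed model (abbreviated GLM in the article) is to "estimate the marginal differences in proportions of no use of all five low-value practices between the study groups". The next sentence gives the fallback: "If the GLM models do not converge, logistic regression with a clustered-robust standard error (hospital level) will be used to calculate odds ratios". Nothing says that these odds ratios will be turned back into differences.

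Table 3 sets the objectives that the models serve. The one for the composite outcome, set for 2019 and for 2018, begins: "The difference between control and intervention group hospitals in the proportion of infants presenting to hospital with bronchiolitis who received care that adhered with all". A parallel objective asks for the same difference for each of the five practices separately, in the same two years.

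The parent-trial result is also reported on the absolute scale, in percentage points (section The PREDICT Bronchiolitis KT Study): "14.1% adjusted risk difference, 95% CI, 6.5-21.7". Intervention adherence there "was 85% (95% CI, 82.6-89.7%) in the intervention group hospitals". For the control figure the text reads "compared with 73% (95% CI, 65.3-78.8%) in the control group hospitals".

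**The concern.** The objective and the main model are on one scale, and the fallback is on another. This is not a detail left for a later analysis plan. The protocol names the replacement measure, and that measure does not answer the question in Table 3.

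Two things are at stake. First, where a model fails, the reader gets an odds ratio in place of the planned difference in percentage points with its interval. Second, convergence is decided model by model. Table 3 implies (1 composite + 5 practices) × 2 years = 12 group comparisons, so one results table could hold differences in some rows and odds ratios in others. Those rows could not be compared across practices or between 2018 and 2019 without further calculation.

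**Working it through.** **Inputs.** Adherence in the parent trial was 85% (intervention) and 73% (control), with a 95% CI for control of 65.3% to 78.8%. The adjusted risk difference was 14.1 points. All are in the section The PREDICT Bronchiolitis KT Study. The protocol gives no projected figure for the group comparison in 2018 or 2019, so these trial results serve as the example.

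**What the sample size rests on.** The Sample size section gives ICC 0.11, a coefficient of variation of cluster size of 0.16, and 12 hospitals of 150 infants.
- Design effect = 1 + ((1 + 0.16²) × 150 − 1) × 0.11 = 17.81.
- Half-width = 1.96 × √(0.85 × 0.15 / 1800 × 17.81) = 0.0696.

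This reproduces the stated 7%. The calculation concerns one group's proportion, so the fallback for the group comparison does not enter it.

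**One pair of proportions on two scales.**
- Difference: 85 − 73 = 12.0 points.
- Odds ratio: (0.85/0.15) / (0.73/0.27) = 5.667 / 2.704 = 2.10.

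**A fixed odds ratio at other control rates.** With control rate p0, the intervention rate is p1 = 2.096·o / (1 + 2.096·o), where o = p0/(1 − p0).

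| Control rate | Intervention rate | Difference (points) |
|---|---|---|
| 65.3% (lower CI limit) | 79.8% | 14.5 |
| 73% | 85.0% | 12.0 |
| 78.8% (upper CI limit) | 88.6% | 9.8 |

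**A fixed difference of 14.1 points at the same control rates.**
- 65.3%: (0.794/0.206) / (0.653/0.347) = 2.05.
- 73%: (0.871/0.129) / (0.73/0.27) = 2.50.
- 78.8%: (0.929/0.071) / (0.788/0.212) = 3.52.

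Within the control group's own confidence interval, then, one odds ratio covers differences from 9.8 to 14.5 points, and one difference covers odds ratios from 2.05 to 3.52. Control hospitals were given a workshop and intervention materials after the trial (Table 1), so their rate may move between the two audit years. If it does, the odds ratio can change while the difference does not, and the reverse.

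**Can the fallback model return the planned measure?** Yes. From the logistic fit, predict each infant's probability with group set to intervention and then to control, average each set, and subtract. The delta method with the hospital-clustered covariance matrix gives the interval. With group as the only term, the model reproduces the two raw proportions, so the standardised difference equals the raw difference. One simulated data set illustrates this (12 hospitals of 150 per group, beta-binomial, true rates 85% and 73%, ICC 0.11). The cluster-robust logistic fit gave an odds ratio of 3.11 (95% CI 1.77 to 5.45). The same fit, standardised, gave 21.0 points (11.1 to 30.9), equal to the raw difference of 21.0. The values are illustrative only. They show that the fallback model does not require a change of measure.

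**The case against.** The strongest reply is that little depends on this. The model and its fallback serve only the exploratory objectives. The primary outcome is the 2019 composite proportion in intervention hospitals, the secondary outcomes are also within-group proportions, and the Data analysis section reports group proportions with 95% CIs in any case. The fallback may never be used. All of this stands, and it limits the weight of the point without removing the mismatch.

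Several stronger readings are tempting, and the documents do not support them:

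- *The sustainability verdict is at risk.* The seven-point margin is applied to each hospital's change from its own post-implementation result. It uses neither the mixed model nor the fallback.
- *The results could not be compared with the trial's 14.1 points.* No aim, outcome or Table 3 objective sets up that comparison. A crude difference in the composite can still be read from the group proportions. Only an odds ratio standing alone cannot be set against 14.1.
- *The target moves from a population-averaged to a hospital-specific effect.* It does not. Logistic regression with cluster-robust errors is still population-averaged, and only the summary scale changes.
- *Rarely used practices, such as adrenaline, will be the ones to fail.* The documents give no use rates for single practices and no evidence about convergence. Which models might fail is unknown.
- *The intervals will be too narrow with so few hospitals.* The protocol neither specifies nor excludes a small-sample correction, and that choice is commonly left to the analysis plan.
- *Odds ratios will be misread as relative risks.* The plan does not say that they will be read that way.

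**Conclusion.** The point holds as a mismatch within the exploratory group comparisons: Table 3 asks for differences in proportion, and the fallback reports odds ratios. Where a model fails, the loss is the planned model-based difference with its confidence interval. If only some models fail, consistency across the 12 comparisons is lost as well. At the parent trial's rates the choice of scale matters: an odds ratio of 2.10 stands for anything from 9.8 to 14.5 points over the confidence interval of the control rate. This rests on two assumptions: that at least one mixed model fails to converge, and that the fallback is followed as written. Control rates in 2018 and 2019 are unknown, and the parent trial's rates stand in for them. No primary or secondary result changes. The point is minor in reach, but it is worth correcting because the remedy costs almost nothing.

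**What to change.** In the fallback sentence, replace the closing phrase about calculating odds ratios with: *to obtain marginal differences in proportions by standardisation (predictive margins), with 95% CIs from hospital-level cluster-robust standard errors; odds ratios may be given in addition.* Apply this to the composite and to each of the five practices, in both years, so that every comparison is reported on the scale of Table 3.

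The cost is one sentence and a little extra analysis work in standard software. It needs no new data, no change of model and no change of sample size.

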#### Sample size

The sample size for this medical record audit will depend on the number of participating hospitals and will be recalculated upon completion of the hospital recruitment stage. Based on our previous study [4], assuming an Intra-cluster Correlation Coefficient of 0.11, an expected proportion of no use of all five low-value practices) of 85% (based on results of the PREDICT Bronchiolitis KT Study) [4] and a Coefficient of Variation of cluster sizes of 0.16 [4], a total sample size of 1800 (obtained from 12 intervention hospitals (clusters) with an average size of 150 infants) will achieve a confidence interval (CI) half-width of 7% (95%CI: 78 to 92%). An equivalent number of infants, i.e. 1800 in total, will also be obtained from ~ 12 control hospitals (clusters) with an average size of 150 infants.

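### The fallback for the exploratory between-group contrasts names no small-sample correction on about 24 hospitals; in its usual form its 95% intervals cover about 92-93% for the composite, and less for rare practices

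*Protocol article*

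**What the plan says.** The quantitative Data analysis section uses a generalised linear mixed model to "estimate the marginal differences in proportions of no use of all five low-value practices between the study groups". It then fixes a fallback for the case of non-convergence, in which "logistic regression with a clustered-robust standard error (hospital level) will be used to calculate odds ratios". Nothing is said about a small-sample version of that standard error or its reference distribution.

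The Sample size section plans a sample "obtained from 12 intervention hospitals (clusters) with an average size of 150 infants", and an equal number that "will also be obtained from ~ 12 control hospitals (clusters) with an average size of 150 infants". The calculation is made "assuming an Intra-cluster Correlation Coefficient of 0.11".

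Table 3 (Exploratory objectives) lists the contrasts. Besides the composite they include the single practices one by one, in an entry that begins "The difference between control and intervention group hospitals in the proportion of infants presenting to hospitals with bronchiolitis who received care that adhered with each". With 2018 and 2019 taken separately, that is (1 + 5) x 2 = 12 between-group contrasts. The fallback sentence follows the composite model directly; I read it as covering the single-practice contrasts too, since no other model is given for them.

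**The concern.** A cluster-robust variance is built from hospital-level residuals, so its quality depends on the number of hospitals and not on the 3,600 infants in a year. With 12 hospitals per group it is biased downward, because the residuals are taken around a mean estimated from the same hospitals. It is also noisy, so a normal quantile is too small. Both effects narrow the interval. When a practice is rare and its use is concentrated in a few hospitals, a sample that misses those hospitals understates both the rate and its variance, and the shortfall grows.

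At stake is how readers would take the intervention-control comparisons for single practices if they came from the fallback: intervals labelled 95% that cover less, and apparent differences that occur too often by chance.

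**Working it through.** **Inputs from the protocol.** 12 hospitals per group, mean size 150, ICC 0.11, coefficient of variation of cluster size 0.16, and expected adherence of 85% (Sample size); control adherence of 73% in the earlier trial (Background).

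**Inputs assumed.** For single practices, use in 1-10% of infants and ICC 0.02, 0.05 or 0.11. The protocol gives none of these.

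**The plan's own figure.** Design effect = 1 + ((0.16² + 1) x 150 - 1) x 0.11 = 17.81. Half-width = 1.96 x sqrt(0.85 x 0.15 x 17.81 / 1800) = 6.96%, which matches the stated 7%. That figure is for the single-group proportion and is not in question here.

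**The fallback's variance.** With group as the only covariate, the robust variance of a group's log odds is

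sum over hospitals of (y_j - m p)² / (k m p(1 - p))²,

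with k = 12 and m = 150, and the two groups' variances are added. The usual form multiplies by G/(G-1) = 24/23 and uses 1.96. Removing the bias from estimating each group's mean needs 12/11, and the matching reference is t on 24 - 2 = 22 degrees of freedom (2.074).

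**Quick analytic check.** The usual form holds a fraction (11/12) x (24/23) = 0.957 of the variance it should. The effective cut-off on a t scale is 1.96 x sqrt(0.957) = 1.917, and P(|t22| > 1.917) = 6.8%.

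**Simulation for the composite** (beta-binomial, ICC 0.11):
- With no true difference, the false-positive rate is about 7-7.5% in the usual form. With the 12/11 factor and t on 22 df it is 5.1-5.5%.
- At 27% v 15% use, with unequal cluster sizes and 40,000 replicates, coverage is 92.7% in the usual form (92.2% with no factor at all). It is 94.6% with CR2 and t(22), and 95.5% with CR3 and t(22). The mean standard error in the usual form is about 5% too small.
- With 13 hospitals per group, coverage is 92.1-92.6% without a small-sample correction. With 100 per group it is 95%, so the small number of hospitals is the cause.

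**Simulation for single practices** (no true difference; coverage in the usual form):

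| Use of practice | ICC 0.02 | ICC 0.05 | ICC 0.11 |
|---|---|---|---|
| 10% | 92.9% | 92.5% | 91.7% |
| 5% | 92.5% | 91.3% | 89.2% |
| 2% | 91.8% | 88.7% | 83.9% |
| 1% | 89.9% | 85.6% | 81.6% |

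As false-positive rates, use of 3%, 2% and 1% gives about 9%, 11% and 14% at ICC 0.05, and about 8-10% over the same range at ICC 0.02. With the 12/11 factor and t(22) together, the ICC 0.05 figures fall to about 7%, 9% and 11%. CR2 or CR3 with t(22) covers 85-94% at 1% use, depending on the ICC. At 1% use, one group has no events in 0.1-10% of samples, and the odds ratio then cannot be estimated.

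**Permutation of hospital labels.** The rejection rate was 3.4-5.0% in one set of runs. A repeat with 1,000 data sets per setting gave 3.1-5.6%, which is at or below 5% within simulation error.

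**Cost in width.** (2.074/1.96) x sqrt((12/11)/(24/23)) = 1.08.

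**The case against.** The strongest objection is that the protocol does not say the standard error is uncorrected. The term it uses also covers bias-corrected versions, and an analysis plan that is not shown may specify one. This stands as a limit: the figures describe the usual form, not one the protocol commits to. It does not remove the point. The protocol names the estimator and the number of hospitals, and with that number the choice of version decides whether the interval is a 95% interval.

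Second, the contrasts are exploratory, and no test or significance level is stated for them. This stands. A reader might infer that false differences will be declared in 9-14% of comparisons, but the plan contains no such decision rule. The firmer statement is about coverage.

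Third, a reader might infer that rare practices are where the mixed model fails, so that the fallback is used exactly where it performs worst. The documents do not show this. In a check with a plain random-intercept logistic model, about 300 data sets per setting, the model converged in all data sets at 15% use (ICC 0.11) and at 3% and 2% use (ICC 0.05). At 1% use it converged in 99.3%, leaving out samples with an empty group. A model with another link or more terms could fail more often, but the claim cannot be made from what is at hand.

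Fourth, the larger figures rest on assumed use rates and ICCs. This stands, which is why they are given as a range.

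**Conclusion.** The point holds as a limited one. In its usual form the fallback undercovers by 2 to 3 percentage points for the composite, on the protocol's own inputs. For practices used in 1-2% of infants the shortfall runs from about 3 to 13 points, but only under assumed use rates and ICCs.

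It would be wrong to infer that the main conclusions are at risk. The primary outcome is a proportion within intervention hospitals, and sustainability is judged by a seven-point rule against each hospital's own earlier result. Neither uses this standard error. The fallback also applies only on non-convergence. The change is worth making because it is cheap and the exploratory intervals will be read as 95% intervals.

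**What to change.** In the quantitative Data analysis section, specify for the fallback a bias-corrected cluster-robust variance (for example CR2 or CR3) with a t reference on the number of participating hospitals minus 2 degrees of freedom. The Sample size section already foresees a recalculation once hospital recruitment is complete, so the degrees of freedom can be fixed then. The cost is one sentence and intervals about 8% wider.

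For rarely used single practices, also report a permutation test that re-allocates hospital labels between the groups, and present the interval with a statement that its coverage may still be below 95%. The test follows the original random allocation of hospitals and can still be computed when one group has no events. Its cost is a second method for some outcomes, and by itself it gives a test and no interval. The use rate below which it applies should be fixed before the data are seen.
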